**Results:**

In September and October 2015, we trained 60 CHEWs and a total of 60 nurses and midwives from 12 local government areas (LGAs) in Kaduna and 23 LGAs in Ondo. Recruitment took place between November 2015 and December 2016. Data analysis is being finalized, and results are expected in March 2018.

**Conclusions:**

The strength of this study is having a standard care (nurse and midwife provision) group with which CHEW provision can be compared. The intervention builds on existing training and supervision procedures, which increases the sustainability and scalability of CHEW implant provision. Important limitations include the lack of randomization due to nurses and midwives in Nigeria working in separate types of health care facilities compared with CHEWs, and that providers self-assess their own practices. It is unfeasible to observe all procedures independently, and observation may change practice. Although providers will be trained to conduct implant removals, the study time will be too short to reach the sample size required to make noninferiority comparisons for removals.

**Trial Registration:**

ClinicalTrials.gov NCT03088722; https://clinicaltrials.gov/ct2/show/NCT03088722 (Archived by WebCite at http://www.webcitation.org/6xIHImWvu)

## Introduction

In 2012, an estimated 222 million women had an unmet need for modern contraception [1]. Meeting this need would avert an estimated 218 million unintended pregnancies and 118,000 maternal deaths [1]. Nigeria has a large (191 million in 2017) and rapidly increasing population [2] and a high maternal mortality ratio, estimated to be 576 per 100,000 live births in 2013 [3]. In 2013, 15% of currently married women aged between 15 and 49 years were using some method of contraception, a figure considerably lower than the global (63%) and sub-Saharan Africa (27%) estimates for the same year, and 16% had an unmet need for contraception [3].

There are many inequities in contraceptive access, with lower levels of use among women in rural and remote areas, and among those who are poorer, less educated, and younger [4]. In Nigeria, contraceptive prevalence is just 9% in rural areas versus 27% in urban areas [3]. In addition, the most effective contraceptive methods are often the most difficult to access [5]. Long-acting reversible contraceptives (LARCs), such as intrauterine devices (IUD) and implants, are the most effective reversible methods of contraception, with failure rates of between 0.05% and 0.8% in the first year of use (contraceptive pills have a failure rate of 8%) [6]. LARCs also have lower discontinuation rates than short-term methods (such as the pill, injectable, and condom) [5] and generally have high user satisfaction [7]. In sub-Saharan Africa, unlike Asia and North America, short-term contraceptive methods dominate [8]. In Nigeria in 2013, 9.8% of currently married women were using a modern method of contraception, and most (7.1%) were using short-term methods; just 1.1% were using an IUD and 0.4% an implant [3].Contraceptive implants consist of flexible matchstick-sized rods, inserted below the skin on the nondominant upper arm. They release small amounts of progestin hormone to prevent pregnancy for 3 to 5 years [9]. Insertion is quick and does not require pelvic examinations or laboratory tests. Complications are rare (although may include infection at the insertion site, expulsion, or difficult removal), and once inserted, implants require no regular action by the user or health system [6].

Key barriers to LARC use include lack of availability (of method or skilled providers), perceived cost, and misperceptions about risks and benefits [5,10,11]. Low LARC availability has been driven by lack of trained providers and, in the case of implants, high commodity costs [12]. In recent years, costs have fallen [13] but low provider numbers remain: the African continent faced an estimated shortage of 4.2 million health care workers in 2013 [14]. Shortages are more acute in rural areas: whereas the national average number of doctors per 100,000 population in Nigeria was estimated to be 12 in 2007, in the more rural northwest and northeast, the ratio was only 4 [15]. Task-shifting or task-sharing is a strategy recommended by the World Health Organization (WHO) to address health worker shortages [16]. This involves expanding specific tasks, where appropriate, from highly qualified health workers to those with shorter training and fewer qualifications [17]. Task-sharing of implant services has been implemented in several African countries [12]. After a policy change allowed nurses, as well as physicians, to provide implants in Tanzania, insertion rates increased from around 10,000 per quarter in 2007 to more than 20,000 in 2009 [18], and in Ethiopia, 15,000 rural community health extension workers (CHEWs) have been trained to insert implants (removals are still handled by higher-level cadres) [12].

In 2012, Nigeria’s Honorable Minister of Health announced a goal to increase contraceptive prevalence to 36% by 2018 [19]. The priority activities are to train more health care workers to provide injectables, implants, and IUDs [19] and to change national policy to permit CHEW provision of implants [20]. CHEWs are health care staff who undergo a 36-month course in a training institution approved by the Community Health Practitioners Registration Board of Nigeria [20]. CHEWs may be located in larger urban health centers, with nurses and midwives, or at smaller health centers, working alone or with another CHEW. In a pre- and posttest pilot study conducted in Sokoto and Bauchi States in Nigeria to assess the feasibility of training CHEWs to provide implants [21], 166 CHEWs were trained for 2 to 3 weeks, and they inserted 3588 implants in 151 health facilities over 6 months. Most CHEWs achieved competency in implant insertions after insertions with 4 to 5 clients. Clinical observations revealed that CHEWs performed implant insertion tasks correctly at least 90% of the time for 16 out of 19 checklist items. The amount of information that CHEWs provided clients increased between baseline and end line, and over 99% of surveyed clients reported being satisfied with CHEWs’ services.

Making implants more widely available could reduce the unmet need and contribute toward achieving the ambitious 2020 contraceptive prevalence rate goals (the percentage of women of reproductive age who are married or in union and are currently using or whose sexual partner is currently using a modern method of contraception) set by many countries in Africa and elsewhere at the family planning (FP) summit in 2012 [22]. A systematic review of the effectiveness and safety of task-sharing for the delivery of injectable contraceptives, contraceptive implants, IUDs, tubal ligation, and vasectomy in low- and middle-income countries found little or no difference between cadres, but admitted that only limited conclusions could be drawn from the small number of eligible studies [23]. The conclusion of this review and the recent policy change in Nigeria mean that there is opportunity and need to evaluate the safety, quality, and acceptability of implant services provided by CHEWs in Nigeria.

## Methods

### Study Design, Aim, and Objectives

The aim of this quasi-experimental, noninferiority study was to compare insertion of contraceptive implants (Implanon Classic and Jadelle; Table 1) by CHEWs with nurses and midwives in Nigeria.

The primary objective was to compare the safety of implant insertions by CHEWs with that of midwives and nurses on the day of the procedure and up to 14 days post insertion. Secondary objectives were to: (1) compare the quality of implant insertions by CHEWs with that of midwives and nurses; (2) compare client acceptability of implant insertions by CHEWs with that of midwives and nurses; and (3) assess acceptability of CHEW provision of implants to other health staff, clinic managers, and other key individuals such as policy makers.

For the purpose of this study, *safety* refers to implant insertions that minimize risk and harm to service users. We hypothesize that implant provision by CHEWs will be as safe and of high quality as provision by existing cadres of implant providers. Safety will be assessed by comparing rates of any adverse events (ie, those with a minor, moderate, or severe impact on a woman’s health) at the time of the procedure, or up to 14 days post insertion (Table 2). As the study is evaluating the provider and not the method itself, method-related adverse events such as hormone-related changes to menstruation pattern, headaches, and nausea will not be recorded; neither will the study examine the effectiveness of the method.

We define *quality* as the degree to which a provider or facility meets certain objective and subjective levels of health care delivery standards. The term covers all aspects of clinical service provision such as correct insertion, infection prevention, and disposal procedures, as well as pre- and post counseling and taking a client-centered approach. We define *acceptability* as the level of satisfaction experienced with the service received (in the case of the client) and the level of satisfaction with this aspect of the job (in the case of the provider).

### Study Implementation

This study is a partnership between Marie Stopes International (MSI); Marie Stopes International Organisation Nigeria (MSION); the Federal Ministry of Health of Nigeria (FMOH); Kaduna and Ondo State Ministries of Health, Nigeria; the WHO’s Department of Reproductive Health and Research Geneva; and the University of Ibadan, Nigeria. Clinical training and research components will be conducted by MSI and MSION. MSION established its first clinic in Abuja in 2009 and now serves women in 25 states. Its mission is to provide reliable information to women about their FP options and to improve their access to FP methods. MSION is one of the only providers of LARCs in Nigeria. Services are delivered through clinics, mobile outreach teams, a social franchise network of private providers, and partnerships with government providers.

### Site and Provider Selection

The study will take place in public sector facilities in 2 Nigerian states, 1 in the north (Kaduna) and 1 in the south (Ondo). The north and south of Nigeria differ in religious beliefs, contraceptive prevalence rate, and availability of health care providers, making it necessary to generate evidence in each context. We will purposively select local government areas (LGAs) in Kaduna and Ondo States for study participation by excluding LGAs with overlapping interventions and, given the extensive supervision needs of the study, hard-to-reach LGAs.

Facilities will be eligible if they provide referral services on site or are located within 20 km of a referral facility, in case of adverse events resulting in the need to refer clients; if there is a provider interested in participating in the study who expects to be in the facility for the 12-month period of client recruitment; and if the facility has been providing FP in the previous 3 years and does not currently provide implants. Larger urban centers staffed by nurses, midwives, and CHEWs and smaller rural health centers staffed by a nurse or midwife only will be eligible for inclusion.

A total of 60 facilities will be selected in each state from eligible facilities, yielding a total of 120 facilities. Where there are more than the required number of eligible facilities, simple random sampling will be used to select facilities for inclusion. At least 30 nurse or midwife-led facilities will be selected in each state to allow inclusion of 30 nurses and midwives in the study. The remaining 30 facilities will include as many CHEW-led facilities as possible. From each CHEW-led facility, 1 CHEW will be trained, and 1 nurse or midwife or 1 CHEW will be trained from each nurse or midwife-led facility. The providers trained will be the individuals responsible for providing FP services at their facility.

**Table 1 table1:** Details of implant brands to be included in the study.

Product	Composition	Labeled duration of use	Format
Jadelle	150 mg levonorgestrel, 2 rods	5 years	2 rods, separate disposable trocar
Implanon Classic	68 mg etonorgestrel, 1 rod	3 years	1 rod preloaded in trocar

**Table 2 table2:** Implant insertion adverse events to be recorded.

Description of adverse reaction		Day recorded relative to procedure
Anaphylactic reaction to the implant		0
Implant insertion unsuccessful on first or second attempt		0
Implant breaks		0
Palpitations resulting from the local anesthetic		0
Expulsion of implant		14
Paresthesia due to neural damage (numbness, tingling, tickling, pricking, or burning sensation at implant site)		14
Pain post procedure for >1 week and requires further outpatient observation and medical intervention		14
**Infection**		0
	Local redness swelling	14
	Discharge	14
	Fever	14
Scarring		14
Hematoma or bruising requiring medical intervention		0 and 14
Bleeding around the injection area		0 and 14
Other adverse reaction requiring medical treatment or resulting in long-term incapacity or fatality		0 and 14

### Intervention Implementation

The intervention will have 4 phases, which are discussed below.

#### Clinical Supervisor Training

A total of 12 clinical supervisors (qualified nurses or midwives with extensive experience of implant service provision) will be trained over 3 days. Training will cover how to train study providers to provide implants, clinical supervision of study providers, and the research study and data collection procedures.

#### Provider Training in Implant Provision and the Research

Clinical supervisors will train providers on counseling and on insertion and removal of Implanon Classic and Jadelle. Training will comprise classroom and clinic components and include a written test. Training will be based on the FMOH’s competency-based training package for LARCs. This involves working with providers at different levels to bring them up to the same level, and so the number of days of training can vary [24]. The implant clinical training materials, previously only used to train nurses and midwives, will be reviewed and adapted if necessary for CHEWs. Training will be free for providers.

All providers will be trained on the study protocol for managing adverse events, which is based on MSI’s adverse event standard operating procedures. The protocol details when to refer clients to a higher-level provider, particularly important for CHEWs who may be working in clinics without a higher-level provider, and adverse event support and reporting mechanisms. Any major adverse event must be reported immediately to the MSION clinical services manager, who will inform the study manager and the MSI medical development team in London within 24 hours. For this study, moderate adverse events will also be reported to the clinical services manager who will inform the study manager. Reportable adverse events are shown in Textbox 1. Other conditions are to be reported if the level of adversity is judged to be persistent or difficult to manage. The clinical services manager will be responsible for ensuring any adverse event reported is managed effectively.

MSION research staff will train providers on the research study, including participant recruitment and consent, data collection, and data storage. Full training (implant provision and research) is expected to take approximately 8 days.

#### Supervised Provision

After training, the trainee can provide implants to clients at their clinic only in the presence of a MSION clinical supervisor.

The trainee will encourage FP clients to attend on scheduled days when the supervisor is present. Clients will be counseled on the available methods, and if they choose an implant, they will be given the option of Jadelle or Implanon Classic. Supervision visits will take place every 2 weeks but exact timings will depend on the volume of implant clients. After 5 successful supervised insertions of each brand of implant, the trainee is accredited to insert implants without clinical supervision.

Moderate and major adverse outcomes to be reported to ensure participant safety.Moderate level of adverse eventPartial expulsion of implant, putting the woman at risk of pregnancyPain at insertion site continues for more than 1 week and requires further outpatient observation and medical interventionBleeding that does not stop and requires a transfer to receive medical careInfection that persists after 7 days of antibiotic treatment (may require implant removal)Major level of adverse eventComplete expulsion of the implant resulting in pregnancyPalpitations from the local anestheticBleeding that requires hospital care or results in long-term health impactsInfection that requires hospital care or results in long-term health impactsParesthesia that requires hospital care or results in long-term health impactsScarring that requires hospital care or results in long-term health impactsAnaphylactic response to the implant

MSION staff will conduct demand-generation activities in the local area to increase awareness of the range of contraceptive methods available, including implants, to ensure that trainees have sufficient clients. Activities may include in-facility awareness raising on special days such as antenatal care, immunization, and child welfare days, and recruiting designated locals to encourage potential clients in their communities to attend the nearest study facility for FP.

On the basis of MSION’s previous experience of conducting training and supervision of midwives, nurses, and doctors, it is expected that most providers will have been accredited for insertion by the end of their first supervision visit. Additional visits will be undertaken in cases where accreditation of insertion is not achieved within the prescheduled supervision visit.

#### Unsupervised Provision

After accreditation, participating providers will start to offer unsupervised implant services in their clinics and to recruit clients to the study. Participating providers will be invited to attend a monthly study meeting at the state level where they will receive study updates and tools and, if necessary, additional training. Providers will receive lunch and travel costs. Supervision visits will still occur but they will be less often following provider accreditation.

### Participant Recruitment and Eligibility

Women requesting an implant from a participating facility will be eligible to participate if they are aged between 18 and 49 years and are eligible to have the implant. On presenting at a participating clinic, each client will be provided with comprehensive FP counseling and offered all available FP methods (balanced counseling technique) [25]. Participating providers will invite all clients who request an implant, and meet the inclusion criteria, to participate in the study, using a study information sheet and consent form. If the client chooses an implant, she will be offered Jadelle or Implanon Classic, and the same service provider will do the insertion. Clients who want an implant but do not want to participate in the study will be advised of the nearest available facility providing this service.

Clients will be recruited until the sample size is reached (anticipated to be approximately 7 months). Participants who are asked to return for a 2-week follow-up visit will be reimbursed for their travel costs. Women who do not return after 14 days will be contacted by telephone (if they gave consent to be contacted and a phone number). In total, 3 attempts will be made to contact women by telephone before they are considered lost to follow-up. Those who are contacted by phone will be asked to attend the facility for the 14-day follow-up visit or, if unable, to answer questions over the telephone.

The number of clients who refuse to take part and who withdraw will be documented, along with the reason for refusal or withdrawal where given. If they agree, very basic sociodemographic data and the reason for refusal will be recorded.

All health care staff at participating facilities will be eligible for participation in semistructured in-depth interviews to assess acceptability of CHEW implant provision. A range of staff types (doctors, nurses, midwives, and CHEWs) will be approached by a senior research staff member and asked for their willingness to participate. Policy makers involved in FP will be contacted individually by researchers and asked to participate in an interview. All participants will be asked for their informed consent before the interview.

### Sample Size

#### Day of Insertion

Calculation of the number of participants required for the study is based on the primary outcome—the frequency of adverse events associated with insertion on the day of the procedure.

Studies documenting adverse events of implant insertion on the day of procedure have found them to be rare. For example, a randomized clinical trial of 2008 women found that 0.2% clients using Jadelle and 0.8% clients using Implanon Classic experienced complications at insertion [26].

To detect a difference in proportion of adverse events between the 2 study arms with a noninferiority limit of 0.5%, 80% power, and 95% confidence level on the day of implant insertion, we would require a sample size of 2462 in each study arm, giving a total sample size of 4924. To account for possible clustering, we will include a design effect of 1.5, increasing the sample size to 7386. To allow for incomplete records, we will increase this by 10% to a total sample size of 8125.

We estimate that each provider will receive approximately 10 insertion clients per month and that we may see a refusal rate of 20%. With a total of 120 providers, we expect to recruit 1200 clients per month. We would therefore need to recruit clients for approximately 7 months to achieve the required sample size for insertions.

#### By Day 14

We expect the number of adverse events observed by day 14 to be higher than that at day 0 as we may start to see infections. This reduces the required sample size needed to detect a difference between health care provider types. To detect a difference in proportion of adverse events between the 2 study arms with a noninferiority limit of 1%, 80% power, and 95% confidence level 14 days after implant insertion, we would require a sample size of 1225 in each study arm, giving a total sample size of 2450. To account for possible clustering, we will include a design effect of 1.5, making the size 3675. Assuming 20% loss to follow-up makes a total sample size of 4410. If we expect to recruit 1200 clients per month, it will take around 4 months to recruit the sample size we require.

All recruited clients will be asked to return to the inserting provider for a follow-up visit at 14 days post insertion until the sample size of 4410 is reached.

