#### Quality and Acceptability of Implant Provision

To detect a difference in the quality and acceptability of implant provision between the 2 study arms, assuming that each group would score an average of 80% of quality and acceptability indicators being met, with a noninferiority limit of 10%, 80% power, and a significance level of 5%, we will need 198 observations in each group. Adjusting for 10% incompleteness, we need 220 in each group (440 total). Assuming a design effect of 1.8 requires a minimum of a total of 792 observed implant insertions. There will be approximately 10 providers per supervisor. So, assuming approximately 10% of insertions can be observed (and client acceptability measured through exit interviews), this equals 812 insertions, which is sufficient according to the sample size calculation.

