### Data Analysis

Quantitative data will be analyzed using statistical software Stata, version 13 (Stata Corp. College Station, Texas). Complete case analysis will be conducted. For safety monitoring, complication rates by provider will be generated by the study manager in Abuja every 3 months, to identify any providers with unusually high complication rates. These data will be checked and response activities will be agreed at the 3 monthly technical advisory committee meetings to be held in Abuja, which will be attended by staff from MSION and MSI, and ministry of health officials.

Training and supervision data will be presented using descriptive statistics. Insertion adverse events of CHEWs will be compared for noninferiority against the complication rates of nurses and midwives. To assess the equivalence between the nurses and midwives and the CHEWs, the risk difference between the 2 provider types together with their 95% CI will be derived by use of a generalized estimating equation model to adjust for clustering. If the CI of the risk difference between the 2 groups falls within the predetermined margin of equivalence (–2% to 2%, which is equivalent of lower bound of one side 97.5% CI), the 2 types of service providers can be considered equivalent.

Sensitivity analysis will be designed to control for group assignment bias among the 2 states. They will be analyzed both separately and together to identify any differences in performance between CHEWs in the northern state compared with the southern state.

All quality and acceptability indicators will be weighted equally, except for those most critical (infection prevention, correct clinical technique, and advice on where to go in case of problems), which will be given a higher weight. The difference in mean quality and acceptability scores between CHEWs and midwives will be compared using a *t* test.

Analysis of qualitative data will be undertaken manually or using a qualitative analysis software such as N-Vivo. Quotations will be labeled by cadre of speaker, and a thematic analysis will be carried out. Transcripts will be read and reread. Extracts will be coded according to themes and subthemes that emerge from the data or that have been identified before the analysis such as those included in the in-depth interview guide. A selection of quotes representing different cadres and views will be used to write a report structured around these themes.

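### The sample sizes appear to rest on a one-sided 5% test but safety is judged with a 95% CI (one-sided 2.5%), so the stated 80% power probably does not describe the decision rule at either of the article's margins

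*Protocol article*

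**What the plan says.** The protocol article sizes three comparisons and states 80% power for each.

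- **Sample Size, Day of Insertion:** "noninferiority limit of 0.5%, 80% power, and 95% confidence level on the day of implant insertion". The result is "we would require a sample size of 2462 in each study arm, giving a total sample size of 4924". The text cites a trial in which "0.2% clients using Jadelle and 0.8% clients using Implanon Classic experienced complications at insertion", but names no planning rate. Inflation follows: "we will include a design effect of 1.5, increasing the sample size to 7386" and "To allow for incomplete records, we will increase this by 10% to a total sample size of 8125".
- **Sample Size, By Day 14:** margin 1%, again 80% power and a 95% confidence level, and "we would require a sample size of 1225 in each study arm". The rate is said only to be higher than on day 0.
- **Sample Size, Quality and Acceptability of Implant Provision:** 80% of indicators met in each group, margin 10%, 80% power, 5% significance, and "we will need 198 observations in each group".

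None of the three says whether the error rate is one-sided or two-sided.

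The Data Analysis section derives a 95% CI for the adverse-event risk difference from a GEE model and compares it with limits of −2% and 2%, "which is equivalent of lower bound of one side 97.5% CI". The Abstract also uses −2%. Quality and acceptability scores are compared by a t test, with no interval level or sidedness given.

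**The concern.** A noninferiority sample size delivers its stated power only if the analysis uses the same error rate and the same margin as the calculation. A 95% confidence level in the sizing and a 95% CI in the analysis look like the same thing, but the published sizes fit a one-sided 95% level, while the analysis names a one-sided 97.5% level. If so, the safety rule is stricter than the one that was sized. Truly equal cadres would then miss the sizing margins more often than the 20% of the time that 80% power implies.

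The margin differs as well: 0.5% and 1% in the sizing, 2% in the decision rule. A reader therefore cannot tell which rule the 80% belongs to.

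**Working it through.** **Formula.** Per-arm size for noninferiority of two proportions with equal true rates p, margin d and 1:1 allocation:

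n = 2p(1−p)(z_α + z_β)² / d², with z_β = 0.842 for 80% power.

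**Step 1: reproduce the plan's figures at one-sided 5%.** (1.645 + 0.842)² = 6.185.

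- Quality (p = 80% and d = 10%, both stated): 0.32 / 0.01 × 6.185 = 197.9, so 198. Matches.
- Day 0 (d = 0.5% stated; p = 0.5% assumed, the midpoint of the cited 0.2% and 0.8%): 0.00995 / 0.000025 × 6.185 = 2461.7, so 2462. Matches. With unrounded z values the result is 2461.
- Day 14 (d = 1% stated; p = 1% assumed): 0.0198 / 0.0001 × 6.185 = 1224.7, so 1225. Matches.

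**Step 2: the same inputs at one-sided 2.5%.** With z_α = 1.96 the sizes are 252, 3124 and 1555. None matches.

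**Step 3: other readings.**

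- At one-sided 2.5%, the stated safety sizes require rates of 0.394% (day 0) and 0.787% (day 14). Rounded rates of 0.4% and 0.8% give 2502 and 1246, which are close but not exact.
- For quality the rate is stated, so no such freedom exists: one-sided 2.5% gives 252, not 198.
- For day 0, a superiority formula for 0.5% against 1% gives 3681 to 5065, and a two one-sided tests formula gives 3408 or 4182. Neither fits.

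**Step 4: power of the 95% CI rule at the sizing margins.** Power = Φ(d / √(2p(1−p)/n) − 1.96). I use n before inflation, taking the design effect of 1.5 and the allowances for missing data as correct.

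- Day 0, p = 0.5%, n = 2462: SE = √(0.00995/2462) = 0.002010; 0.005/0.002010 − 1.96 = 0.527; power 70.1%.
- Day 14, p = 1%, n = 1225: SE = √(0.0198/1225) = 0.004020; 0.01/0.004020 − 1.96 = 0.527; power 70.1%.

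The planning rates are assumptions, so the range matters:

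| Time point and margin | Assumed rate | Power with 95% CI |
|---|---|---|
| Day 0, 0.5% | 0.2% | 97.5% |
| | 0.4% | 79.4% |
| | 0.5% | 70.1% |
| | 0.8% | 50.4% |
| Day 14, 1% | 0.5% | 93.9% |
| | 0.8% | 79.3% |
| | 1% | 70.1% |
| | 2% | 42.4% |

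**Step 5: power at the 2% margin of the decision rule.**

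- Day 0, p = 0.5%: 0.02/0.002010 − 1.96 = 7.99; power above 99.9%.
- Day 14, p = 1%: 0.02/0.004020 − 1.96 = 3.01; power 99.9%. If both limits must lie inside ±2%, it is 2 × 0.9987 − 1 = 99.7%.
- Day 14, p = 2%: 94.2%, or 2 × 0.9424 − 1 = 88.5% for both limits.

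**Step 6: quality.** With 198 per group, SE = √(0.32/198) = 0.0402, and 0.1/0.0402 − 1.96 = 0.527. On the plan's own proportion-based calculation, a two-sided 5% test has 70.1% power, and a one-sided 5% test has the stated 80%.

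**The case against.** The strongest reply is that 70% is not the power of the rule as written. The Abstract and Data Analysis decide against 2%, where power exceeds 99% at the inferred rates. A reader might infer that the study carries a 30% chance of an inconclusive safety result when the cadres are equal. The documents do not support that: it holds only at the sizing margins and the inferred rates, and at 2% the chance is below 1%. This part of the reply stands.

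A reader might also infer that all three sizes can arise only from a one-sided 5% test. That is shown for 198 alone. The safety rates are not stated, and rates near 0.4% and 0.8% would nearly reconcile the safety sizes with the 95% CI. One pair of constants yields all three published integers, with a day-0 rate at the midpoint of the cited values, so one-sided 5% is the best-fitting reading for safety, but it remains an inference.

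Nor does the 95% CI rule cover quality and acceptability, which go to a t test of unstated sidedness on mean scores. A 5% significance level can be one-sided, so no contradiction is shown there. The gap is that the sidedness which makes 198 sufficient is not stated.

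Finally, the mismatch is conservative: the analysis alpha is stricter than the sizing alpha, so false claims of noninferiority do not rise. That is correct, and it is why the remedy is restatement. It does not make the stated power right.

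**Conclusion.** The point holds in this form. One-sided 5% is certain for the quality size and the best-fitting reading for the two safety sizes, while safety is judged at one-sided 2.5%. If the planning rates were 0.5% and 1%, the 95% CI rule has about 70% power at margins of 0.5% and 1%, and more than 99% at 2%. On those rates the stated 80% describes the decision rule under neither margin. If the rates were 0.4% and 0.8%, power at the sizing margins is about 79%, close to what is claimed, but the article does not say so.

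The margin conflict is the larger inconsistency, and final power cannot be fixed until it is resolved. For quality, 198 per group supports a one-sided 5% test only. The figures assume equal true rates, 1:1 allocation and a correct design effect.

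**What to change.** 1. Use one noninferiority margin per safety endpoint, the same in the Abstract, Sample Size and Data Analysis. As recruitment is over and analysis is being finalized, show that the margin was fixed before the outcome data were seen.
2. State the planning event rates for day 0 and day 14 and the one-sided alpha.
3. Keep the 95% CI (one-sided 2.5%). Moving to a 90% CI to match the sizing would loosen the rule after data collection.
4. Restate power for that margin and alpha, with a range over plausible rates: about 70% if 0.5% and 1% are kept with rates of 0.5% and 1%. For reference, 80% power would then have needed 3124 and 1555 per arm before inflation, that is 3124 × 2 × 1.5 × 1.10 ≈ 10,310 in total against 8125, and 1555 × 2 × 1.5 × 1.20 = 5598 against 4410.
5. State the sidedness of the quality and acceptability comparison so that it matches the 198 calculation, or restate its power (about 70% if two-sided 5%).

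This changes text only and needs no extra clients. The cost is a less favourable power statement if the sizing margins are kept.
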